**LIST OF ABBREVIATIONS AND RELEVANT DEFINITIONS**

| **ABR** | **ABR form, General Assessment and Registration form, is the application form that is required for submission to the accredited Ethics Committee (In Dutch, ABR = Algemene Beoordeling en Registratie)** |
| --- | --- |
| **AE** | **Adverse Event** |
| **AR** | **Adverse Reaction** |
| **CA** | **Competent Authority** |
| **CCMO**  **CHD** | **Central Committee on Research Involving Human Subjects; in Dutch: Centrale Commissie Mensgebonden Onderzoek**  **Congenital heart disease** |
| **CV** | **Curriculum Vitae** |
| **DSMB**  **fECG** | **Data Safety Monitoring Board**  **Fetal Electrocardiogram (in Dutch: foetaal electrocardiogram)** |
| **GCP** | **Good Clinical Practice** |
| **GUO IC** | **Advanced ultrasound research. In Dutch: Geavanceerd ultrageluid onderzoek Informed Consent** |
| **METC**  **MMC**  **SD**  **SEO** | **Medical research ethics committee (MREC); in Dutch: medisch ethische toetsing commissie (METC)**  **Máxima Medical Center**  **Standard deviation**  **Structural ultrasound research (in Dutch: structureel echografisch onderzoek)** |
| **SPC** | **Summary of Product Characteristics (in Dutch: officiële productinfomatie IB1-tekst)** |
| **Sponsor** | **The sponsor is the party that commissions the organisation or performance of the research, for example a pharmaceutical**  **company, academic hospital, scientific organisation or investigator. A party that provides funding for a study but does not commission it is not regarded as the sponsor, but referred to as a subsidizing party.** |
| **Wbp** | **Personal Data Protection Act (in Dutch: Wet Bescherming Persoonsgevens)** |
| **WMO** | **Medical Research Involving Human Subjects Act (in Dutch: Wet Medisch-wetenschappelijk Onderzoek met Mensen** |

**SUMMARY**

**Rationale:** Congenital heart disease (CHD) is a severe condition, which needs early detection and treatment. The current method for detecting CHD during pregnancy is a structural ultrasound around week 20 of gestational age. Only 25 to 60 per cent of the cases are detected by this method. Therefore, there is need for a technique with a higher sensitivity, in order to guarantee early detection. This new technique could be the transabdominal non-invasive fetal electrocardiogram (fECG). In order to detect the different abnormalities, the normal ranges of amplitudes and segment intervals of the fECG have to be established.

**Objective**: To detect the normal range of amplitudes, segment intervals and the heart axis of the fECG. To compare fECG of healthy fetuses and fetuses with severe CHD.

**Study design:** This study will be performed as a cross-sectional and a case-cohort study. The first part of the research (cross-sectional study) focuses on the normal range of amplitudes and segment intervals of the fECG. The second part (case-cohort study) will focus on the values of the amplitudes and segment intervals of fetuses with diagnosed a severe CHD like Fallot’s tetralogy. CHD is diagnosed by the current method for prenatal screening, the structural ultrasound. The center, at which the CHD is diagnosed, informs the patient about our study and contacts us if the patient is willing to participate in the study. Centers involved in this research are the tertiary care hospitals: Máxima Medical Center Veldhoven (MMC), University Medical Center Utrecht (UMCU), Radboud Medical Center Nijmegen (UMCN), Acadamic Medical Center Amsterdam (AMC).

**Study population:** In the cross-sectional study, 200 pregnant patients, aged older than 18 years, with a gestational age of 18 – 24 weeks will be included. The fetuses have to be healthy, without any known congenital heart abnormalities. For the case-cohort study, the fetus must be diagnosed with a severe, hemodynamic important CHD. We will include 10 patients with the same sort of severe CHD. The types of CHD we will include are: Fallot’s Tetralogy, hypoplastic left heart syndrome, aortic stenosis, pulmonary atresia, transposition of the great vessels, coartcation of the aorta and an atrial ventricular septal defect

**Intervention**: The fECG is a non-invasive, transabdominal approach with self-adhesive electrodes. The recordings are performed between 08.00 h and 16.00 h during appointments at the outpatient clinic and will take no longer than 45 minutes. The patient will be lying on a comfortable bed in a semi-recumbent position.

**Main study parameters/endpoints:** to determine the normal values and ranges of amplitudes, segment intervals and heart axis of healthy fetuses with a gestational age of 18 to 24 weeks. To establish the differences in fECG between healthy fetuses and fetuses diagnosed with severe CHD.

**Nature and extent of the burden and risks associated with participation, benefit and group relatedness:** There is no risk associated with the recordings of the fECG. There might be some minor skin irritation caused by the self-adhesive electrodes. Measurements are combined with regular hospital visits.

# 1. INTRODUCTION AND RATIONALE

During pregnancy, multiple ultrasound examinations are performed to assess the fetal condition. This is executed, amongst others, during or around week 20 of gestational age and is called the fetal anomaly ultrasound (SEO in Dutch). With this technique, all kind of possible congenital anomalies can be detected, including CHD. However, a false negative diagnosis occurs frequently and the SEO only detects 25 to 60 per cent of the patients with CHD^1, 2^. That makes CHD the most common structural fetal abnormality of which a significant part is missed during the prenatal life.

CHD can be divided into cyanotic and non-cyanotic. An example of cyanotic CHD is Fallot’s tetralogy or a transposition of the great vessels. An example of the non-cyanotic form is an aortic stenosis, atrial septum defect or an aortic coarctation. The incidence of CHD is estimated to be 4 to 9 per 1000 live born^3^. In the Netherlands, the overall incidence of anomalies of the vascular system is estimated at 6,6 per 1000 live births^4^. The incidence of severe CHD (read, of hemodynamic importance) is low (see appendix I. page 27).

The survival for patients with CHD is low, 21 percent^2, 3^, and the prognosis is negatively influenced by the presence of heart failure, aneuploidy or extracardial malformations. There are several studies which show a correlation between an abnormal heartbeat of the fetus and the diagnosis CHD. These patterns can be diagnosed with ultrasound (including the Doppler technique), which is the current method for prenatal screening of CHD. If a CHD is suspected or seen on the SEO, the patient will receive a more intensive ultrasound, named the GUO (geavanceerd ultrageluids onderzoek) in Dutch. If the CHD is confirmed with the GUO, the fetus has a high certainty of having a CHD. In 2003, the Dutch magazine of medicine (in Dutch: Nederlands tijdschrift voor geneeskunde) reported a sensitivity of 94,7%, a specificity of 98,8%, a positive prognostic value of 95,3% and a negative prognostic value of 98,6%^5^

However, these routine controls with ultrasound can only diagnose about 25 to 60 per cent of the large heart defects^1, 2^. The disadvantage of Doppler ultrasound is that there can be false – negatives. Plus the fact that Doppler can’t detect beat – to – beat heart rate, which causes several heart abnormalities to be missed.

The medical world needs a reliable non-invasive diagnostic method with a better detection rate of CHD. However, up till now, a transabdominal non-invasive fECG was too difficult to accomplish. Velayo et al^2^ was the first to report the clinical possibility of using fECG to detect CHD in 2011. They conducted a prospective study with a total of 179 women with singleton pregnancies from 18 to 41 weeks of gestation. All patients received an ultrasound investigation and a fECG on the same day. They found a sensitivity of 100% and a specificity of 99% of the fECG for detecting CHD. It is possible that after combining the fECG with the ultrasound, the sensitivity and specificity will be even higher.

Most forms of CHD have an abnormal fECG^5^. The most important aspect of the ECG is the heart axis, for example right axis deviation. This is seen in most of the severe CHD forms, like Fallot’s tetralogy. Other possible abnormal aspects of the fECG are amplitudes and segment intervals (prolonged or premature).

Researchers of the Máxima Medical Center (MMC) and the Eindhoven University of Technology are working in collaboration to develop the fECG^1,6^. The fECG can be performed non-invasively during pregnancy^7^. Like the fetal anomaly ultrasound, it can be used from 18 weeks of gestational age onwards. As stated above, CHD will most likely be marked by fECG changes^5^.

The first difficulty of conducting a fECG is that the fetus is surrounded by amniotic fluid and maternal tissues, which enlarges the distance to the electrodes. Second, the fetus moves around, which makes it difficult to measure the heart from one single direction. On top of that, at a gestational age of 20 weeks the fetal heart is about 1/10^th^ of the size of an adult heart^6^.

The fECG during pregnancy is difficult to interpret. The main reason for this is a physiological dominance of the fetal right ventricle during pregnancy. This is caused by the circulation of the fetus in utero. Thus, right-sided obstructive lesions such as Fallot’s tetralogy or pulmonary hypertension with a dominance of the right ventricle are difficult to diagnose in utero. These right-sided obstructive lesions are usually accompanied by left-sided obstructive lesions such as aortic stenosis or coarctation of the aortae^8^. Because of the difficulty of diagnosing right-sided obstructive lesions, the lesions combined with left-sided obstruction can be detected more easily.

We expect that the fECG can detect severe heart conditions early in pregnancy, with the possibility of adequate early treatment in the future. Nowadays, there are options of operating during pregnancy to optimize the outcome of the fetus with CHD.

We hypothesize that the non-invasive fECG combined with the SEO has a higher detection rate for diagnosing CHD compared to the SEO alone. We expect that the fECG can detect additional details about the development and etiology of CHD. More knowledge about fetal heart rhythms and abnormalities of the different intervals and heart axis in a fECG are needed to optimize the diagnosis and management of CHD.

The summary of the most occurring ECG findings of the most common CHD can be found in Appendix II, page 28.

# 2. OBJECTIVES

Primary Objective: To establish the normal ranges or values of amplitudes, segment intervals (with 95% confidence intervals) and the heart axis of the fECG in a healthy fetus.

Secondary Objective: To compare the fECG in various forms of severe CHD with the “normal” fECG. To determine the diagnostic value of fECG to detect CHD.

# 3. STUDY DESIGN

Both the cross-sectional and case-cohort study are prospective in nature. In the future, a longitudinal cross-sectional study can be performed based upon this study.

The cross-sectional study will take place in the MMC, Veldhoven, the Netherlands and Diagnostic center Eindhoven, the Netherlands. All the patients who visit the outpatient clinic for the first time will receive information about the research. Patients who visit the Diagnostic center Eindhoven will receive information about the research via their appointment confirmation e-mail. Measurements will be performed before or after the SEO or GUO-1 after written informed consent; patients do not have to come to the hospital or the diagnostic center for an extra visit.

The case-cohort study will take place in the MMC Veldhoven, and the medical centers Radboud MC Nijmegen, Academic Medical Center Amsterdam, and Maastricht UMC the Netherlands. Whenever a patient is diagnosed with a fetal severe CHD in any of these centers by using the SEO and the GUO, they will inform the patient about our research and contact us after informed consent. We will perform a fECG during routine follow up visits in those centers. For more information on recruiting the patients, see chapter 9, paragraph 9.2 “Recruitment and consent”.

In the cross-sectional study, 200 pregnant women will be included. With this amount of patients, we can determine with the wanted accuracy what the normal values and 95% CI of a healthy fetus are^9, 10^. If any of these fetuses is diagnosed with a CHD, they will automatically be evaluated in the case-cohort study.

In the case-cohort study, we will include pregnant women carrying fetuses with a form of severe CHD, preferably with the same CHD. A severe CHD is defined as possibly life threatening and/or needing intervention or surgery in the first year of life. For now, we believe that of every CHD, we need 10 patients to determine the difference between the normal values and the segment intervals of the fetuses with this severe CHD. The overall incidence of CHD is 4 to 9 per 1000 living newborns^4^. Because of this low incidence, it would take years to include more than 10 fetuses per form of severe CHD. Because of this reason, plus the fact this concerns a pilot study, we chose to include 10 fetuses per form of severe CHD. Because of this low incidence, collaboration with more than one center is needed. We believe that we will be able to collect data of the fECG of 10 fetuses with the support of the other centers.

The fECG signals are stored and digitized by a program named the NEMO system^1^. More details can be found in chapter 4.

With the collected data, we will perform several sub-analyses. We will calculate the normal values and ranges of the amplitudes (P, QRS, T), and the segment intervals with 95% confidence intervals. We will also evaluate the heart axis of the fetus. This data will be compared with the collected data of the fetuses with CHD. The patients will not be notified of any abnormal findings on the fECG, because this contains a pilot study and any findings on the fECG are still being evaluated. Therefore, this research does not have any consequences for the standard care plan of the patients and their fetuses.

If any of the fECG turns out to be abnormal, it will not influence the treatment of the fetus. The main reason for the last fact is that we do not know if the findings we think are abnormal are actually abnormal. This is one of the aspects we would like to investigate.

In the future, a longitudinal research is needed to determine the sensitivity and specificity of fECG.

Approximately 10 weeks postpartum, the patients from the cross-sectional study will receive a questionnaire about their delivery and their newborn and patient information can be withdrawn from the postnatal clinic or the attending pediatrician. If the participants do not return the questionnaire, they will be excluded from further analyses.

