# STUDY POPULATION

## 4.1 Population (base)

In the cross-sectional study, 200 pregnant women carrying a healthy, singleton fetus with a gestational age between 18 and 24 weeks, who visit the outpatient clinic in MMC Veldhoven or Diagnostic center Eindhoven, will be included. If any of the fetuses turn out to have a form of CHD, the data will be either excluded or analyzed in the case-cohort study.

In the case-cohort study, pregnant woman carrying a singleton fetus, with a gestational age between 18 and 24 weeks, with a known severe CHD will be included. We will include patients with the following CHD: Fallot’s tetralogy (possible with pulmonary atresia of stenosis), hypoplastic left heart syndrome, aortic stenosis, transposition of the great vessels, coartcation of the aorta and atrial ventricular septal defect. We chose these types because they are severe and have hemodynamic consequences if they do not get the proper treatment. Because of the low incidence of these types of CHD (see appendix I page 27), we believe it is impossible to gather more than 10 patients per CHD. Therefore, we will include 10 patients in every CHD group, leading to a total of 60 patients with 6 different forms of severe CHD. We believe that we will include 20 patients per participating center, thus 2 forms of CHD in every center. We believe this will be enough to detect any big differences between the fECG of the healthy fetuses and the fECG of the fetuses with CHD, but we are aware that more research will be needed in the future. Because the incidence in our medical center is low, collaboration with more than one center is needed.

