## 9.2 Recruitment and consent

The patients of the cross-sectional study will be recruited through the gynecology outpatient clinic and through the Diagnostic center Eindhoven. The patients will receive information about the research during the appointment at the outpatient clinic, when the SEO or GUO-1 will be planned or via e-mail with the confirmation of their appointment for a SEO at the Diagnostic center Eindhoven. This information contains all the aspects and details of the research. Attached to the patient information letter, the patients will find an informed consent form. If patients have any questions, one of the researchers will answer these questions. Before the fECG will be conducted, the researcher will explain the meaning of the research again. The time of consideration will vary between different patients.

The patients of the case-cohort study will be recruited after the SEO and they will have recently discovered that their baby has a form of severe CHD. The follow up will be provided by a gynecologist at MMC Veldhoven, Radboud MC Nijmegen, AMC Amsterdam or Maastricht UMC. These specialists will ask the patients if they want to join the research. They will receive the information letter. Attached to the patient information letter, the patients will find an informed consent form. If wanted, the researcher can provide some extra information before conducting the fECG. It is important to conduct the fECG before week 24. The time of consideration will vary between different patients.

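### Fetuses enrolled as CHD cases on prenatal ultrasound are not re-checked after birth, although healthy-group status is, so each form group of 10 may contain misclassified fetuses

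*Protocol*

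**What the plan says.** **Check after birth.** Protocol section 3 states that "the patients from the cross-sectional study will receive a questionnaire about their delivery and their newborn", and allows information to be obtained from the postnatal clinic or the paediatrician. Section 6.3 describes the same procedure, again for the cross-sectional study, with the purpose of learning whether those fetuses were born healthy. A newborn found to have CHD that the structural ultrasound (SEO) missed leaves the healthy group and is evaluated with the cases. Section 8 uses the questionnaires only to judge whether cross-sectional data can be kept. Section 6.4 says that there are no follow-up moments.

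**How a case is established.** Section 3 has the participating centres diagnose severe CHD "by using the SEO and the GUO". The Summary names one test only: "CHD is diagnosed by the current method for prenatal screening, the structural ultrasound". Section 9.2 says: "The patients of the case-cohort study will be recruited after the SEO".

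**Accuracy of the confirming test.** For the GUO, section 1 cites a source that "reported a sensitivity of 94,7%, a specificity of 98,8%, a positive prognostic value of 95,3" per cent, and a negative predictive value of 98.6%.

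**Size and analysis of the case group.** Section 4.1 says that "we will include 10 patients in every CHD group", "leading to a total of 60 patients with 6 different forms of severe CHD". Section 8 puts fetuses with the same form in one group and compares each with the healthy group. Section 3 defines severity partly by the need for intervention or surgery in the first year of life.

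**The concern.** The protocol accepts that a prenatal label needs checking after birth, and acts on this for the healthy fetuses. For the positives it does not, although it cites a predictive value below 100%. Part of its own definition of severe CHD, intervention or surgery in the first year, can be confirmed only after birth, and nothing collects that information for the cases.

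Two kinds of error are possible, and they act differently:

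- A fetus enrolled as a case that has no CHD would be expected to dilute its group's difference from the healthy group.
- A fetus with CHD of another form blurs the form-specific patterns that section 8.2 names as the secondary parameter. It need not pull the group mean towards normal.

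With 10 fetuses per form, one wrong label is a tenth of a group. The case group would also mix standards, because the few cases that cross over from the healthy group under section 6.3 are ascertained after birth and the others are not. An analysis plan cannot repair this, since it concerns diagnoses that nobody is asked to collect.

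**Working it through.** **Inputs, all from the protocol**

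- Cases: 6 forms × 10 = 60. This reproduces the total in section 4.1.
- GUO accuracy (section 1): sensitivity (Se) 0.947, specificity (Sp) 0.988, positive predictive value (PPV) 0.953, negative predictive value (NPV) 0.986.

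**Step 1: are the four accuracy figures consistent?** The prevalence *p* implied by Se, Sp and PPV is

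p = PPV(1 − Sp) / [PPV(1 − Sp) + Se(1 − PPV)] = 0.011436 / (0.011436 + 0.044509) = 0.204.

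Then NPV = Sp(1 − p) / [Sp(1 − p) + (1 − Se)p] = 0.7861 / (0.7861 + 0.0108) = 0.986, which equals the cited value. The figures agree with one another, and they describe a population in which about 20% had the condition.

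**Step 2: expected false positives if the cited PPV applies**

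- Among 60 cases: 60 × (1 − 0.953) = 2.82.
- At least one in a given group of 10: 1 − 0.953^10 = 0.382.
- At least one among 60: 1 − 0.953^60 = 0.944.
- The exact binomial distribution puts 97.8% of its probability on 0 to 6 false positives among 60.
- The Summary and section 4.2 list pulmonary atresia separately, which makes seven forms. Then 70 × 0.047 = 3.29.

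**Step 3: sensitivity to the pre-test risk.** Se and Sp are kept as cited. The pre-test risks other than 20.4% are assumptions. PPV = Se·p / [Se·p + (1 − Sp)(1 − p)].

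| Pre-test risk | PPV | Expected false positives, 60 × (1 − PPV) | At least one in a group of 10, 1 − PPV^10 |
|---|---|---|---|
| 10% | 0.898 | 6.1 | 66% |
| 20.4% (implied) | 0.953 | 2.8 | 38% |
| 40% | 0.981 | 1.1 | 17% |
| 60% | 0.992 | 0.5 | 8% |

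**Step 4: effect on a form group.** Let the true mean shift be δ. If one of 10 fetuses has no CHD and a normal fetal ECG, the expected group shift is 0.9δ. On average, at the cited PPV, it is 0.953δ.

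**Errors in form.** The protocol gives no rate for a correct finding of CHD with the wrong form, so no figure can be derived.

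**The case against.** The strongest case on the other side has five parts.

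1. *The cases are verified.* Section 3 requires the GUO as well as the SEO, and section 1 treats the GUO as the confirming test. A reader might infer that case status is never checked; that is too strong. The gap is confirmation after birth, and CHD discovered after birth in the cross-sectional group is an exception even to that.
2. *The cited PPV may not carry over.* The title of the cited source concerns congenital anomalies in general, and the figures imply a prevalence near 20%. Under section 1 a fetus reaches the GUO because CHD was suspected or seen on the SEO, so its pre-test risk may be higher and false positives fewer. This stands. It is tempting to state that about 3 of the 60 cases will be false positives, but the documents support only a conditional figure within a range.
3. *The effect is small beside sampling error.* For a true shift of 1 SD, one normal fetus in 10 costs 0.10 SD, while the standard error of a mean of 10 is 1/√10 = 0.32 SD. The case comparison is a declared pilot without a sample size calculation, looking for large differences. This stands as a limit on severity. It does not remove the point, because the number of wrong labels would stay unknown.
4. *No accuracy estimate is at risk.* A reader might infer that the study's estimate of fetal ECG sensitivity will be too low. Section 2 does mention diagnostic value, but section 3 leaves sensitivity and specificity to later research and section 8 computes neither.
5. *The sections do not really conflict on the entry test.* Recruitment after the SEO, in section 9.2, describes timing and is compatible with a GUO in between. Only the Summary is loose. A reader might infer that some cases enter on the SEO alone; section 3 speaks against this, though the Summary should not leave it open.

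**Conclusion.** The point holds as a gap in data collection for the secondary comparison. Cases enrolled on SEO plus GUO are not re-checked after birth while the healthy fetuses are, so the groups are held to different reference standards.

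The expected number of false positives is 2.8 of 60 if the cited PPV applies to these cases, and 0.5 to 6.1 for assumed pre-test risks of 60% down to 10%. Both rest on the cited sensitivity and specificity and on entry through the GUO. They are expectations, not predicted counts, and the 38% chance per group of 10 is conditional in the same way. Errors in form would come on top, at a rate that the protocol does not allow anyone to estimate.

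The primary objective, normal ranges in healthy fetuses, is not affected. The change should be made because it is cheap and because every comparison by form depends on the labels.

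**What to change.** - **Sections 3 and 6.3:** extend the existing postnatal record retrieval to every case (newborn diagnosis or surgical report, or post-mortem report where available), and add this to the case consent.
- **Section 8:** group cases by final diagnosis where it is available. Keep cases that have a prenatal diagnosis only, and flag them. Because that main analysis still mixes two standards, repeat the comparison by prenatal diagnosis and in confirmed cases only.
- **Reporting:** give the number of cases that change group, the number that prove not to have CHD, and the resulting number per form.
- **Summary:** align the diagnostic wording with the SEO-plus-GUO entry standard in section 3.

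**Cost:** one record request per case, at centres already following these women, and a line in the consent form. No extra visit or procedure is needed. Some form groups may end with fewer than 10 fetuses once cases are reclassified, and the protocol should say that this is accepted.
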